### Implementation outcomes

In addition to the aforementioned effectiveness outcomes, implementation outcomes include Reach, Adoption, Implementation and Maintenance. Reach is measured on both patient and GP (practice) level, while adoption, implementation and maintenance are measured at GP level in the intervention group. Quantitative data will be obtained from project records, medical records, and decision tool logs. Qualitative data will be obtained through semi-structured interviews with GPs in the intervention group during and after the trial. The interviews will explore GPs’ experiences with the diagnostic strategy, including barriers, facilitators, and reasons for its use or non-use in terms of adoption, implementation and maintenance, as well as their experiences with and reasons for using or not using the implementation strategies. We will use an inductive approach to thematic saturation [53], guided by sensitizing concepts derived from the literature. Qualitative data collection stops when thematic saturation is reached, defined as the point at which additional interviews no longer generate new information relevant to each implementation outcome.

#### Reach

Reach refers to the representativeness of participating children, GPs and GP practices. Outcome measures include the proportion and demographics of children exposed to the diagnostic strategy (from all eligible children), participating GPs (from all invited GPs), and participating GP practices (from all invited practices). Reasons for non-participation will also be documented.

#### Adoption

Adoption is the proportion of children per GP in the intervention group for whom the diagnostic strategy was used (from all eligible children seen by the GP).

#### Implementation

Implementation refers to adherence to both the intervention and implementation strategies. Outcomes for implementation include the proportion of children per GP in the intervention group for whom the diagnostic strategy was applied as intended (from all children for whom the strategy was used), and the proportion of GPs in the intervention group who used the two main implementation strategies.

#### Maintenance

Maintenance refers to sustained adoption and intervention adherence by GPs two years after inclusion. We will assess this quantitatively using the three-item Provider REport of Sustainment Scale (PRESS), which is a brief and pragmatic outcome measure on the continued use of an evidence-based practice, showing good validity and reliability (Cronbach’s alpha: 0.947) [54].

### Sample size considerations

The prediction rule at a cut-off of 14 points and a CRP value of ≥ 50 mg/l has a specificity of 97% and 94%, respectively [20, 21]. We therefore anticipate an improvement of efficiency from 88% (current care [2]) to 95% (the weighted mean of the aforementioned specificities). To detect the 7% difference in efficiency with 80% power at a two-sided 5% significance level, a cluster size of 3 and an intraclass correlation of 0.01 [55], the required sample size is 510 children without appendicitis (255 per arm). Adjusting for an anticipated 10% loss to follow-up, we aim to include a total of 566 children without appendicitis (283 per arm). Accordingly, we will include all children assessed for appendicitis, including those with appendicitis, until the target sample of 566 children without appendicitis has been reached. Although children with appendicitis do not contribute to the formal sample size calculation for our trial, which is powered for the primary outcome (efficiency), they will contribute to the assessment of the secondary outcome (safety). With an average of two to six children presenting during office hours per general practice in two years [2, 56, 57], we aim to recruit at least 170 GP practices with a mean patient population (85 per arm).

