## Background

Acute abdominal pain is a common reason for doctor consultations in children, accounting for nearly 10% of childhood visits in primary care [1]. More than 90% of these children have self-limiting conditions such as gastroenteritis or constipation [2, 3], whereas 5% have acute appendicitis, the prime reason for referral to secondary care in this population [2, 4–6]. Prompt recognition and referral of children with appendicitis by the general practitioner (GP) is crucial, as perforation occurs in 18% of cases [2] and is associated with high morbidity, including increased risk of postoperative complications (39%), pelvic abscess formation (53%), readmissions (14%) and prolonged hospitalisation [7–12]. Yet timely diagnosis of appendicitis is challenging in primary care, as early symptoms can be atypical and often overlap with those of benign conditions [5, 13, 14]. Moreover, current GP guidelines provide limited support, as they lack explicit referral criteria for appendicitis and do not recommend the use of C-reactive protein point-of-care testing (CRP POCT) due to insufficient evidence [4]. Consequently, 19% of children with appendicitis are not referred during the initial GP consultation, while 70% of those who are referred do not have appendicitis, which can lead to avoidable anxiety, healthcare utilisation and costs [2, 3, 15–18].

Although several prediction rules for identifying appendicitis in children exist in secondary care [13, 19], only one has been developed and validated in a primary care setting [20]. This rule, based on seven routinely available symptoms and signs, stratifies children into low-, medium-, or high-risk groups for appendicitis. External validation demonstrated good discrimination (c-statistic 0.90; 95% CI 0.89–0.92) and good calibration [20]. An additional study showed that CRP adds diagnostic value beyond symptoms and signs and may improve decision making in children with diagnostic uncertainty, corresponding with the medium-risk group of the prediction rule [21].

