### Intervention: diagnostic strategy for appendicitis

GPs in the intervention group use a diagnostic strategy for appendicitis that integrates an externally validated seven-item prediction rule with CRP POCT and risk-based management advice. The prediction rule consists of routinely available signs and symptoms, each assigned a point score (Table 1).

**Table 1 Tab1:** Clinical prediction rule for acute appendicitis

Predictor	Point score
Male sex	2
Nausea/vomiting	2
Pain duration < 24 h	1
Pain duration 24–48 h	2
Elevated temperature ≥ 37.3˚ C	1
Abnormal bowel sounds (absent, tinkling or high-pitched)	1
Right lower quadrant tenderness	5
Peritoneal irritation (abdominal rigidity, guarding, rebound tenderness and/or pain with jarring movements)	4

Based on the total score of the prediction rule, children are stratified into three risk groups: low (0–7 points), medium (8–13 points) and high risk (≥ 14 points) for appendicitis. A sensitivity and specificity for appendicitis of ≥ 95% correspond with the lower (7 points) and upper (14 points) cut-offs, respectively [20]. Management advice is tailored to appendicitis risk (Fig. 1): safety netting is advised for low-risk children, while immediate referral is recommended for those at high-risk. For children in the medium-risk group, GPs are instructed to perform CRP POCT. Based on the CRP value, the strategy recommends either safety netting (CRP < 10 mg/L), reassessment or immediate referral depending on the GP’s clinical judgment and parent/child preference (CRP 10–50 mg/L), or immediate referral (CRP ≥ 50 mg/L). The reassessment is considered a continuation of the initial consultation and includes a repeat clinical assessment and, if indicated, CRP POCT, and should take place later the same day or, if not feasible, the following morning. Cut-offs for CRP were derived from previous primary care research, where CRP ≥ 10 mg/L showed 0.87 (95% CI 0.77–0.94) sensitivity for appendicitis, increasing to 1.00 (95% CI 0.89-1.00) after 48 h, and CRP ≥ 50 mg/L demonstrated 0.94 (95% CI 0.93–0.96) specificity [21].

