### Implementation strategies

As shown in previous research, diagnostic strategies are often not used or used incorrectly by GPs, which can reduce efficiency and increase failure rates [31–33]. We therefore complemented the diagnostic strategy with targeted implementation strategies to improve adherence [34–38]. Prior to study conduct, we identified barriers and facilitators through qualitative research, literature, and stakeholder input using the Consolidated Framework for Implementation Research (CFIR) (Supplementary 3) [39]. Based on these findings, we identified implementation strategies using the CFIR-Expert Recommendations for Implementing Change (ERIC) Matching Tool and developed these into study-specific strategies (Supplementary 4). The two main strategies are online training and a clinical decision tool integrated in the primary care EHR system, based on the ERIC strategies: developing educational materials, promoting adaptability and reminders for clinicians [40–44].

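### The anticipated 95% efficiency is a weighted mean of two specificities, which is not the efficiency of the stepwise pathway, so the effect size behind the 80% power is not validly derived

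*Protocol article*

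**What the plan says.** All references are to the protocol article.

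- **Sample size considerations** starts from two published accuracy figures: "The prediction rule at a cut-off of 14 points and a CRP value of ≥ 50 mg/l has a specificity of 97% and 94%, respectively". It then sets the target: "We therefore anticipate an improvement of efficiency from 88% (current care [2]) to 95% (the weighted mean of the aforementioned specificities". No weights are given.
- The same section builds the power statement on that target: "To detect the 7% difference in efficiency with 80% power at a two-sided 5% significance level", with "a cluster size of 3 and an intraclass correlation of 0.01", leading to "the required sample size is 510 children without appendicitis (255 per arm". After 10% loss this becomes 566. The abstract repeats the 88% to 95% improvement.
- **Intervention: diagnostic strategy for appendicitis** describes a stepwise pathway. Low-risk children are not referred, and high-risk children are referred without CRP. Only medium-risk children are tested. They are referred at CRP of 50 mg/L or more; at 10–50 mg/L the advice is "reassessment or immediate referral depending on the GP’s clinical judgment and parent/child preference".
- **Table 3** defines efficiency as d/(b + d) over all children without appendicitis. It counts referrals at the initial consultation or at planned reassessment.
- **Data analysis** makes intention-to-treat primary, whatever care was actually received.
- **Implementation strategies** reports from earlier research that "diagnostic strategies are often not used or used incorrectly by GPs, which can reduce efficiency and increase failure rates".

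**The concern.** The 97% already covers all children without appendicitis: its complement, 3%, is the share scored as high risk and referred at the first step. The CRP step can only add further false-positive referrals. Averaging 97% with 94% treats the two tests as alternatives applied to separate groups of children, which is not how the strategy works.

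The average also omits two things that the protocol describes. One is the referral of children with CRP 10–50 mg/L, at once or at reassessment; both count as referrals under Table 3. The other is incomplete use of the strategy, which an intention-to-treat comparison carries into the result.

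The 7-point difference is the sole basis of the stated 80% power for the primary outcome. If the true expected efficiency differs by a point or two, the power differs a great deal. A reader of a null or imprecise result would then be working from a power figure that the protocol has not justified.

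**Working it through.** **1. Reproduce the stated sample size.** Inputs from Sample size considerations: 88% v 95%, two-sided 5%, 80% power, cluster size 3, ICC 0.01.

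- Pooled two-proportion formula without continuity correction: n = [1.960·√(2·0.915·0.085) + 0.842·√(0.88·0.12 + 0.95·0.05)]² / 0.07² = 248 per arm.
- Design effect: 1 + (3 − 1)·0.01 = 1.02, and 248·1.02 = 253 per arm. The stated 255 equals 85 practices × 3 children.
- Power at 255 per arm (effective n = 255/1.02 = 250): 80.3%.
- Loss to follow-up: 510/0.9 = 566.7, stated as 566.

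The arithmetic is sound, given 95%.

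**2. What the weighted mean implies.** Solving 97w + 94(1 − w) = 95 gives w = 1/3, so the unstated weights are one third and two thirds. Any such mean must lie between 94% and 97%.

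**3. Efficiency of the pathway.** Among children without appendicitis, let m be the medium-risk share. Let r be the share of medium-risk children who have CRP 10–50 mg/L and are referred. The non-referral proportions are:

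- low risk, share 1 − 0.03 − m: 100%
- medium risk, share m: 1 − 0.06 − r
- high risk, share 0.03: 0%

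The sum is (0.97 − m) + m(0.94 − r) = **97% − m(6% + r)**.

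This assumes that the 94% CRP specificity holds within the medium-risk group, which the protocol does not say. With r = 0, 95% requires m = 2/6, one third. The result can fall below 94%, which no mean of 97% and 94% can do. In the limiting case where every child without appendicitis who is not high risk is tested and r = 0, it is 0.97·0.94 = 91.2%.

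**4. Range.** The protocol gives neither m nor r, so the values below are assumptions. Control efficiency stays at 88%, with 255 per arm, design effect 1.02 and full uptake.

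| m | r | Efficiency | Power |
|---|---|---|---|
| 10% | 0 | 96.4% | 94% |
| 20% | 0 | 95.8% | 89% |
| 10% | 10% | 95.4% | 85% |
| 33.3% | 0 | 95.0% | 80% |
| 20% | 10% | 93.8% | 62% |
| 30% | 5% | 93.7% | 60% |
| 30% | 10% | 92.2% | 35% |

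**5. Uptake.** Suppose 95% held under full use, and the strategy were used for 80% of children (assumed) with usual care for the rest. Efficiency would be 0.8·95% + 0.2·88% = 93.6%, and power 58%.

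**6. Power by efficiency alone.** 92%: 32%. 93%: 48%. 94%: 65%. 95%: 80%. 96%: 91%. Around the target, one point less efficiency costs about 15 points of power.

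**The case against.** The strongest reply is that power is always conditional on an assumed difference. On this view 95% is a reasonable target, the arithmetic is right, and the pathway formula itself returns 95% at m of one third. The weights and risk-group shares may also be in the cited validation work. Part of this stands: 95% is attainable, and the sample-size calculation contains no slip. But the protocol does not present 95% as a target difference. It presents it as the result of a calculation, and that calculation does not match the strategy. Supplying the weights would not repair it, because 97% and 94% are not the efficiencies of two separate groups.

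A reader might go further in three ways that the documents do not support.

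- *That 95% is close to the best the strategy can achieve, or that power is much lower than stated.* The formula tops out at 97%, and a small medium-risk share gives more than 80% power. Without m and r, the direction of the error is unknown.
- *That poor uptake is established.* The remark about non-use describes earlier research and introduces the training and decision tool meant to counter it. Permitted deviation can move efficiency either way. Finding a child later through the records shows a missed invitation, not that the strategy went unused. The 80% uptake is purely illustrative.
- *That referrals for other conditions push efficiency down by a known amount.* The Background says "More than 90% of these children have self-limiting conditions such as gastroenteritis or constipation" and puts appendicitis at 5%. The remainder is therefore anywhere from 0 to 5% (100 − 90 − 5), with no referral rate given. No effect on power can be derived from that.

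**Conclusion.** The concern holds in a limited form. The derivation of the 95% is invalid for the described pathway and the Table 3 definition. It leaves out the CRP 10–50 mg/L route and makes no allowance for incomplete uptake under intention-to-treat. The stated 80% power is therefore unsupported, but it has not been shown to be too high.

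Two directional statements are safe. Referrals through the CRP 10–50 mg/L route can only lower efficiency. If the strategy does better than usual care, partial use with usual care otherwise pulls the result back towards 88%. A medium-risk share below one third works the other way. The 35% to 94% spread in power reflects assumed m and r, the 94% specificity carried into the medium-risk group, and the protocol's own 88%, cluster size and ICC.

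**What to change.** Replace the weighted mean with the pathway calculation among children without appendicitis, using the group's validation data:

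1 − [P(high) + P(medium) × {P(CRP ≥ 50) + P(CRP 10–50) × P(referred)}],

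with the CRP probabilities taken within the medium-risk group. Then dilute the result for expected uptake.

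In Sample size considerations and the abstract, state the resulting efficiency and the power that 255 per arm gives at that value. Add a short table of power over about 92–96%. If the inputs cannot be obtained, call 95% an assumed target difference, drop the weighted-mean justification, and give the same table.

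The cost is one calculation and a wording change. The sample size, primary outcome and analysis model need not change. The downside is that the stated power may become less favourable.

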### Data analysis

#### Clinical effectiveness

We will present descriptive statistics to summarise and compare baseline characteristics of GPs and children between the intervention and control groups. The primary analysis will be on an intention-to-treat basis, i.e. based on the randomised group allocation of the children’s GP practice, regardless of the actual care received. Additionally, a per protocol analysis will be performed, including only children in the intervention group who received the diagnostic strategy and CRP POCT as intended, and children in the control group who did not undergo CRP-testing.

Analyses will be carried out on the individual patient level. Dichotomous outcomes (proportions) will be analysed using logistic mixed-effect regression models with fixed effects for group allocation and practice size, and a random effect for practice to account for clustering of patients within GP practices. Continuous outcomes will be analysed using linear mixed effects regression models with the same approach. When outcomes are measured repeatedly, an additional random effect for patient will be included to account for within-patient correlation, along with fixed effects for time and, if appropriate, its interaction with allocation. If necessary, fixed effects for clinically meaningful differences in baseline characteristics will be included in supplementary analyses. Exploratory analyses will be performed to assess subgroup differences in effectiveness by age and sex through inclusion of the corresponding treatment-by-subgroup interaction terms in the regression models.

Estimates of intervention effects ((adjusted) mean differences or ORs, as appropriate) are presented with 95% confidence intervals (CIs). Adverse health outcomes (e.g. complications in appendicitis cases and non-appendicitis cases, missed other emergency diagnoses) will be summarised descriptively, without further statistical analysis.

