Impact trials of diagnostic prediction rules are rarely conducted in primary care, largely due to their complexity, costs, and duration [22]. Nevertheless, we opted for an RCT to generate the highest possible level of evidence [68]. An additional strength of our study is its pragmatic hybrid type 1 design, which enables simultaneous evaluation of effectiveness and implementation outcomes, supporting direct translation of the study findings into daily practice [69–72]. Further strengths include the use of implementation strategies to optimise adherence, as well as a three-month follow-up period that allows comprehensive assessment of healthcare resource use. We selected referral efficiency as the primary outcome, in line with recommendations by Reilly et al. [22]. Safety was defined as a secondary outcome, as using it as a co-primary outcome would have required an unfeasibly large number of children with appendicitis. Therefore, although the results will provide supportive evidence regarding the safety of the intervention, any observed differences between the arms in this outcome must be interpreted with caution due to the lack of adequate power. There could be some misclassification in diagnosing appendicitis, as there are rare cases of spontaneously resolving appendicitis that might be missed [73]. However, since these cases would not require a referral for surgery, this misclassification will not influence the clinical relevance of our outcome.

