Still, our study has some limitations. First, although the cluster design reduces potential contamination between GPs [74, 75], it can introduce selection bias if GPs in the intervention arm include children with different characteristics (e.g. more severe symptoms) than those in the control group [76]. To address this, missed eligible children are identified retrospectively via GP registries, and their characteristics compared with those of included children for both groups, with adjusted analyses conducted if baseline differences are observed. Second, GPs and patients are not blinded, which may lead to bias. However, we consider this bias to be limited, as pragmatic trials assess overall effects on the care pathway rather than isolated intervention effects [27]. Third, children presenting at out-of-hours primary care service are not included because of logistical constraints related to the inclusion of GPs and children at these services, particularly the training of an unfeasibly large number of GPs and the reviewing of medical records at numerous individual practices within the service’s catchment area. This may limit generalizability of findings to out-of-hours settings due to potential differences in urgency and severity of appendicitis.

In summary, this study will evaluate whether a diagnostic strategy for appendicitis in children presenting to their GP with acute abdominal pain can reduce referrals to secondary care without increasing delayed diagnoses, compared to usual care. If our hypothesis is confirmed, the findings may support its adoption in routine practice, ultimately contributing to more efficient care and better outcomes for these children.

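### The mixed logistic model fixed for safety does not suit about 30 appendicitis cases, nearly one per affected practice, and the safety half of the hypothesis is worded more firmly than such data allow

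*Protocol article*

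**What the plan says.** Under Data analysis, Clinical effectiveness, the protocol article sets one model for every binary outcome: "Dichotomous outcomes (proportions) will be analysed using logistic mixed-effect regression models with fixed effects for group allocation and practice size", with a random effect for practice. The only outcomes there exempted from modelling are adverse health outcomes, which are described without testing. Safety is defined under Secondary outcomes and in Table 3 as a/(a + c), so its denominator is appendicitis cases alone.

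Sample size considerations counts only children without appendicitis: "Adjusting for an anticipated 10% loss to follow-up, we aim to include a total of 566 children without appendicitis (283 per arm". Recruitment stops when that number is reached. Cases are whatever accompany them, and no expected number is given. The Background supplies the prevalence: "whereas 5% have acute appendicitis, the prime reason for referral to secondary care in this population".

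The Discussion explains that safety was not made co-primary because too many cases would be needed. It calls the safety results supportive and warns that "any observed differences between the arms in this outcome must be interpreted with caution due to the lack of adequate power". Its closing summary nevertheless says the study will evaluate whether the strategy "can reduce referrals to secondary care without increasing delayed diagnoses, compared to usual care", and links possible adoption to confirmation of the hypothesis. The abstract's Discussion words the hypothesis in the same way, and the opening of the main Discussion speaks of lower referral rates with safety not compromised. None of these places gives a margin.

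**The concern.** A random practice effect is learned from practices that contribute several observations. If nearly every practice with a case has exactly one, the data hold almost no information on the practice variance, and the estimate can run to zero or to an implausible value. Separately, if every case in one arm is referred, the maximum-likelihood odds ratio is infinite (or zero), and if that happens in both arms it is undefined.

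At stake is the interpretation of delayed appendicitis, the main safety question for a strategy meant to reduce referrals. The planned model may return an unstable odds ratio or none. Because the hypothesis joins fewer referrals to no increase in delayed diagnoses without a margin, a wide, non-significant result could be taken as confirming its second half.

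**Working it through.** **The plan's own figure.** "a cluster size of 3 and an intraclass correlation of 0.01 [55], the required sample size is 510 children without appendicitis (255 per arm". Two proportions, 88% v 95%, two-sided 5%, 80% power, pooled variance: 248 per arm. Design effect 1 + (3 − 1) × 0.01 = 1.02, and 248 × 1.02 = 253, close to the stated 255. Then 510/0.9 = 566.7, which matches 566. The primary sample size is not in question.

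**Expected cases** = non-cases × p/(1 − p).
- p = 5% (Background), 566 non-cases: 566 × 0.05/0.95 = 29.8.
- p = 5%, 510 evaluable non-cases: 26.8.
- Prevalence implied by the article's other usual-care figures (19% of cases not referred at first, 70% of referrals without appendicitis, 88% efficiency): 0.30 = 0.81p/[0.81p + 0.12(1 − p)], so p/(1 − p) = 0.036/0.567 = 0.0635 and p = 6.0%. That gives 566 × 0.0635 = 36 cases, or 32 among 510.

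The range is about 27 to 36 cases. I use 30, or 15 per arm. For an assumed prevalence of 3% to 10% the count with 566 non-cases would be about 18 to 63.

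**Spread over practices.** 30 cases placed at random in 170 practices:
- with at least one case: 170 × [1 − (169/170)^30] = 27.6
- with exactly one: 30 × (169/170)^29 = 25.3
- with two or more: 27.6 − 25.3 = 2.3 (about 3 if practices differ in size)
- cases per affected practice: 30/27.6 = 1.1

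**Behaviour of the planned model.** The random-intercept model was fitted to 400 simulated data sets per scenario (30 cases, latent intraclass correlation 0.01). The practice variance went to zero in 53% of fits with safety of 81% in both arms, and in 50% with 81% v 95%. The practice standard deviation exceeded 3 in about 39% of fits in both scenarios. Fits with no empty cell, no extreme coefficient and no exploded variance made up 54% and 24%.

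**Chance that at least one arm has no missed case** = 1 − (1 − 0.81^15)(1 − s^15), where s is safety with the strategy. Here 0.81^15 = 0.042.

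| s | chance |
|---|---|
| 61% | 4.3% |
| 81% | 8.3% |
| 90% | 24.0% |
| 95% | 48.6% |

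The 81% is 100% − 19%, which covers the initial consultation only, whereas safety also credits planned reassessment. If usual-care safety were 90% (an assumption) and the arms were equal, the chance would be 1 − (1 − 0.90^15)² = 37%.

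**What a null result would mean.**
- 12/15 v 12/15: Newcombe 95% interval for the difference, −28 to +28 points.
- Equal safety of 81%: standard error of the log odds ratio = √[2 × (1/12.15 + 1/2.85)] = 0.93, so an odds ratio of 1 would carry an interval of about 0.16 to 6.2.
- Fisher power for a fall from 81% to 61%: 11%.
- With 12/15 under usual care, 6/15 with the strategy gives p = 0.06. Significance needs 5/15 (p = 0.03).

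**The case against.** Several points on the other side are sound.

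A reader might infer that the model cannot be estimated at all. The figures do not support that. When the variance goes to zero the model becomes ordinary logistic regression, which gives an imprecise arm effect, and on the 81% assumption neither arm is empty in about 51% to 96% of trials. The defect is fragility. The larger risks of an empty cell also arise when the strategy is safer than usual care. Under the harmful scenario of 61% the risk is only 4%.

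A reader might also infer that the low power is concealed, or that the authors intend to read non-significance as safety. Neither is supported. Sample size considerations says the trial is powered for efficiency, the Discussion asks for caution, effects are to be presented with 95% confidence intervals, and no rule equates non-significance with safety. The closing sentence on adoption is hedged and is not a decision rule. Nor is this the only harm outcome: Table 2 and the analysis section provide for adverse health outcomes, described without a model.

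Finally, a fallback for failed fits is ordinary analysis-plan detail, and that plan is not shown. Its absence is not the point here. The article states which model applies to binary outcomes, safety included, and that stated choice is ill-suited whether or not a fallback exists.

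**Conclusion.** The point holds as a mismatch between a stated model and one outcome, together with wording that goes further than the article's own caveat. With about 30 cases (27 to 36) at roughly 1.1 per affected practice, the practice variance is practically unidentified. The probability that at least one arm has no missed case runs from about 4% to 49% for strategy safety of 61% to 95%, and is higher if counting planned reassessment lifts usual-care safety above 81%.

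The Discussion's caveat deals with power but does not change the model, and the abstract and closing summary still attach no increase in delayed diagnoses to the hypothesis without a margin. An interval of about ±28 points cannot confirm that half of it.

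This rests on 5% to 6% prevalence among enrolled children, equal arms, cases falling at random over 170 practices, and 81% as a stand-in for usual-care safety. The primary analysis is unaffected.

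**What to change.** For safety only, replace the mixed model with the counts per arm and a Newcombe or exact confidence interval for the difference in a/(a + c), or with Firth-penalised logistic regression, in either case without a random practice effect. State the expected number of cases (about 27 to 36).

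Align the abstract's Discussion, the opening of the main Discussion and its closing summary with the caveat already given: safety is estimated with its interval, and a non-significant difference will not be reported as confirming no increase in delayed diagnoses.

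Missed appendicitis per enrolled child (c/N) may be added, but descriptively only. It rests on the same 15 × 0.19 = 2.85, or about 3, missed cases per arm. With 566/0.95 = 596 children, 298 per arm, the Newcombe half-width at 3/298 v 3/298 is about 2.0 points. The measure is also sensitive to the differential recruitment that the Discussion lists as a limitation.

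The cost is small: a change of wording, no further children or data, and a more modest safety conclusion. Clustering would be ignored for safety, which matters little at about 1.1 cases per affected practice.
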